### Outcome measurements

#### Primary outcomes

The primary outcomes of the study include the effective rate on the improvement of heart functional class and TCM syndrome. TCM syndrome is evaluated by grading the quantitative score according to the primary symptoms and secondary symptoms. Two indices, which are measured before and after treatment, are simple measurements used to judge the degree of CHF. The severity of heart failure symptoms has a poor correlation with ventricular function, but is clearly associated with survival rate [3].

#### Secondary outcomes

Combined with physical and chemical examinations pre- and post-treatment, changes in objective indices are used to evaluate the therapeutic effect.

LVEF and other echocardiographic indices reflect left ventricular function. In view of the correlation between left ventricular volume, LVEF and angiography on autopsy, the trial uses the modified Simpson method to measure echocardiographic indices, and the relevant standard operating procedure is presented in the investigator’s manual.

The plasma brain natriuretic peptide (BNP) level can be used as an auxiliary method to evaluate the treatment efficacy. Test instruments(Biosite Triage ® MeterPlus) will be unified to avoid measurement error.

The trial will combine the symptoms and signs with X-ray cardiac telephotography examination for assessment of Lee’s heart failure score.

Six-minute walking distance is measured within 24 hours after inclusion and also after treatment to evaluate the change in exercise tolerance. At the same time, the trial also observes the occurrence of end-point events, and analyzes the incidence and readmission rate for cardiovascular events.

#### Safety outcomes

Safety is assessed by vital signs, laboratory examinations and adverse events. Vital signs include blood pressure and heart rate. Laboratory examinations include routine blood and urine, routine stool and fecal occult blood, hepatorenal function, electrolytes and electrocardiogram. The purpose of examining routine stool and fecal occult blood is to prevent gastrointestinal hemorrhage because of the treatment with antiplatelet aggregation, anticoagulant drug. The purpose of examining electrolytes (K^+^, Na^+^, Cl^−^) is to prevent electrolyte disorder for heart failure treatment with diuretics.

Adverse events will be recorded during the treatment. The prognosis of adverse events will also be observed until the adverse reactions disappear or are relieved.

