**Methods:**

This protocol adopts the design of a prospective, randomized, multicenter, blind imitation, placebo-controlled trial to assess the efficacy and safety of Shenfu injection loading in the treatment of patients with acute exacerbation of chronic heart failure due to coronary heart disease. The research will be carried out in 12 hospitals in China and is expected to enroll 160 inpatients with acute exacerbation of chronic heart failure due to coronary heart disease (*yang* and *qi* deficiency syndrome). On the basis of the conventional therapy of western medicine, patients will be randomized to either the treatment group (100 ml 5% glucose injection + 50 ml Shenfu injection) or the control group (150 ml 5% glucose injection) for 7 ± 1 days and follow-up for 28 ± 3 days. The primary outcomes are New York Heart Association cardiac function classification and Traditional Chinese Medicine syndromes. The secondary outcomes are left ventricular ejection fraction, brain natriuretic peptide level, Lee’s heart failure score, 6-minute walking distance, and the incidence and readmission rate of cardiovascular events (including the emergency rate due to acute exacerbation of chronic heart failure).

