### Objective

The objective of this trial is to observe the influence of heart function and TCM syndrome and to assess the short-term effectiveness and safety in patients with AECHF due to CHD (*yang-qi* deficiency syndrome) treated with SFI loading.

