### Interventions

According to *The diagnosis and treatment guideline for AHF of China in 2010* [2] and *The diagnosis and treatment guideline for CHF of China in 2007* [13], doctors will choose medications based on conventional Western medicine treatment, and are prohibited from using other TCM in addition to the test drug. Combined with the cardiac function of patients, the basal therapy for CHF and AECHF are as follows: diuretics (furosemide injection for the first 7 ± 1 days and oral tablet during the follow-up period), angiotensin-converting enzyme inhibitors or angiotensin receptor blockers, β-blockers, aldosterone antagonists, digitalis, anti-platelet drugs, statin drugs, and so forth.

In order to reduce the bias of the test results, the control group is treated with 150 ml 5% GLI. The injection volume for the control group is therefore the same as the treatment group. All patients need to have a fasting blood glucose test and diabetic patients have to adjust the dose of insulin before participating in the trial.

The test drug is used as follows. For the treatment group: 50 ml SFI dissolved in 100 ml 5% GLI delivered via intravenous drip within 150 minutes, once a day; for the control group: 150 ml 5% GLI via intravenous drip within 150 minutes, once a day; both over 7 ± 1 days as a course.

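### The stated adverse-event window is the 7 ± 1 day course, so new non-endpoint adverse events have no stated recording for roughly 68–84% of the time patients are observed

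*Protocol article*

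**What the plan says.** The Objective section sets out "to assess the short-term effectiveness and safety in patients with AECHF due to CHD". The Safety outcomes section gives the collection rule: "Adverse events will be recorded during the treatment". The next sentence adds: "The prognosis of adverse events will also be observed until the adverse reactions disappear or are relieved".

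The length of treatment is fixed in the Interventions section for the two arms alike: "both over 7 ± 1 days as a course". The Methods paragraph of the Abstract gives the two periods together: "for 7 ± 1 days and follow-up for 28 ± 3 days". The Interventions section also keeps them apart when it describes the diuretic: "furosemide injection for the first 7 ± 1 days and oral tablet during the follow-up period".

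Under Secondary outcomes, "the trial also observes the occurrence of end-point events, and analyzes the incidence and readmission rate for cardiovascular events". The Abstract adds emergency visits for exacerbation to that outcome and links follow-up to short-term prognosis.

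**The concern.** The article is not silent on when adverse events are collected. It names a period, and that period is much shorter than the time patients stay under observation. A statistical analysis plan can tabulate only what was collected, so it cannot repair a short collection window.

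What is at stake is the scope of the safety conclusion. Serious cardiac events in follow-up should reach the database through the secondary outcome, but as efficacy data. Other new events that begin after the last infusion have no stated route into it. The Safety outcomes section itself names electrolyte disorder under diuretics as something to watch for, and the Interventions section continues the diuretic through follow-up, so at least one of the plan's own safety concerns outlasts the stated window. A report that calls the treatment safe could be read as covering the whole observation period when the adverse-event data cover about its first week.

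**Working it through.** The article gives no figure for the share of time covered by adverse-event recording, so there is none to reproduce. The check has two parts.

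**1. What the text covers**

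| Type of event | During the course | After the course |
|---|---|---|
| Adverse event starting on treatment | Recorded | Followed until it disappears or is relieved, no calendar limit |
| Cardiovascular event, readmission, emergency visit for exacerbation | Secondary outcome | Secondary outcome |
| Other new adverse event | Recorded | No recording stated in the readable text |

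Only the last cell is empty.

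**2. How much time that cell represents**

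Inputs: treatment t = 7 days, range 6 to 8 (Interventions); follow-up u = 28 days, range 25 to 31 (Abstract, Methods). The text does not say whether u is counted from baseline or from the end of treatment, so both readings are worked.

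*Reading A, u counted from baseline.* Share without stated recording = (u − t) / u.
- Central: (28 − 7) / 28 = 21/28 = 75%
- Smallest: (25 − 8) / 25 = 17/25 = 68%
- Largest: (31 − 6) / 31 = 25/31 = 81%

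*Reading B, u counted from the end of treatment.* Share without stated recording = u / (t + u).
- Central: 28 / (7 + 28) = 28/35 = 80%
- Smallest: 25 / (8 + 25) = 25/33 = 76%
- Largest: 31 / (6 + 31) = 31/37 = 84%

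Over both readings the range is 68% to 84%. If recording ran to the end of follow-up, the share would be 0% under either reading. These are shares of calendar time, not of expected harm; the article gives no data on event timing.

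**The case against.** Several counter-arguments have force.

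- **The text does not say that recording stops.** The word *only* is an inference. Figure 2, which is said to list the work at each time point, is not shown and may contain an adverse-event check at follow-up. This stands, and it limits confidence. It does not remove the point: the Safety outcomes wording would then disagree with the schedule and would need correcting.
- **A treatment-period window for a one-week infusion is a defensible design choice.** The objective promises short-term safety and nothing to day 28. This stands too. A reader might infer that the trial cannot meet its own safety objective; the document does not support that. The objective is served for the course and is simply not shown to be served for follow-up.
- **Efficacy is not generally measured over 28 days.** A reader might see a 28-day efficacy window set against a one-week safety window. In fact both primary outcomes, and most secondary ones, are measured before and after treatment. Only the event and readmission outcome is plausibly tied to follow-up, so the asymmetry is confined to that outcome.
- **Post-course harm is not lost wholesale.** Cardiovascular events, readmissions and emergency visits are captured, and adverse events already open are followed. An arrhythmia counted as a cardiovascular event would be included. End-point events are not defined in the readable text, so it cannot be said that non-cardiovascular deaths go uncounted.
- **Days are not risk.** Drug-related harm may cluster during infusion. This is fair, and it is why the percentages describe coverage and nothing more.

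What survives is the empty cell: new events after the course that are not end-points.

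**Conclusion.** The point holds in a limited form. On the readable text, new adverse events that begin after the last infusion and are not counted as cardiovascular or end-point events have no stated recording for 75% or 80% of observed time, depending on where the 28 days start, and for 68% to 84% across the visit windows.

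This rests on two assumptions: that treatment means the infusion course, as the separate naming of the follow-up period suggests, and that the schedule not shown adds no adverse-event recording at follow-up. The second cannot be checked here, so confidence is moderate.

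The consequence is a safety conclusion that reaches less far than the period of observation. The primary analysis, power and type I error are untouched. The change is worth making because patients are already being followed and the cost is small.

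**What to change.** 1. In Safety outcomes, define the adverse-event window as running from the first infusion to the 28 ± 3 day follow-up in both arms, state whether those 28 days are counted from baseline or from the end of treatment, and reconcile the sentence with Figure 2.
2. Tabulate on-treatment and whole-period events separately. Include in the whole-period table the cardiovascular events, readmissions and emergency visits already collected as a secondary outcome.
3. For patients who have already finished, retrieve post-course events from the follow-up records and the study medical record before database lock, blinded to allocation and by the same procedure in both arms. Report these as retrieved retrospectively, not as prospectively recorded.
4. If retrieval is incomplete, limit the safety conclusion explicitly to the treatment course.

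The cost is a data-entry field and a check of source records. The main drawback is timing: the Trial status section puts the study at database testing, ready for data input, so fully prospective capture may no longer be possible and retrospective capture may be incomplete. No change to sample size or to the efficacy analysis is needed.

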### Data collection

We will collect basic information (gender, age, previous history, medication and so forth), disease severity assessment (heart functional class, TCM syndrome score, Lee’s heart failure score, 6-minute walking distance), and physical and chemical examinations (echocardiogram, BNP and so forth); specific items and study visits are shown in Figure 2.

**Figure 2 Fig2:**
[figure not shown]
**The trial flow chart.** The work at each point of time is listed. cTnT, cardiac troponin T; cTnI, cardiac troponinI; CK-MB, creatine kinase-MB isoenzyme; NYHA, New York Heart Association; TCM, Traditional Chinese Medicine ; LVEF, left ventricular ejection fraction; BNP, brain natriuretic peptide; 6MWD, 6-minute walking distance; FBG, fasting blood glucose; ECG, electrocardiogram; CRF, case report form.

Data information will be separately filled in the study medical record and the case report form by researchers. The study medical record is designed to be convenient for the researchers. Based on the need for data traceability, the study medical record preserves original information, such as the patient’s name, contact information, the results of physical and chemical examinations and so forth. The design of the case report form is convenient for data entry. The patients are distinguished by code, and their personal and private information will not be shown.

### Statistical analysis

Statistical analysis will be performed by the Tianjin Institute of Clinical Evaluation, and the data will be analyzed using Statistical Analysis System (SAS) software version 9.3 (SAS Institute Inc., Cary, NC, USA). Data sets for efficacy assessment will follow the intention-to-treat principle. Continuous variables will be described using mean and standard deviation and tested by *t* tests. Categorical variables will be presented using percentages and tested by chi-squared test. More details will be described in a formal statistical analysis plan.

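### For continuous secondary outcomes measured before and after treatment, the named unadjusted t test is valid but less precise than ANCOVA on the baseline already collected, with BNP on the log scale

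*Protocol article*

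**What the plan says.** The Statistical analysis section sets one method for all continuous data: "Continuous variables will be described using mean and standard deviation and tested by" *t* tests. For the rest it says: "Categorical variables will be presented using percentages and tested by chi-squared test". Neither sentence mentions a baseline covariate, the allocation factors or a transformation. The section then adds: "More details will be described in a formal statistical analysis plan".

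The Secondary outcomes section shows that baseline values exist and points to changes as the quantity compared: "Combined with physical and chemical examinations pre- and post-treatment, changes in objective indices are used to evaluate the therapeutic effect". For exercise tolerance it says: "Six-minute walking distance is measured within 24 hours after inclusion and also after treatment to evaluate the change in exercise tolerance". On BNP it says: "The plasma brain natriuretic peptide (BNP) level can be used as an auxiliary method to evaluate the treatment efficacy", with nothing on its distribution.

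The Randomization section allocates dynamically on age band and cardiac function class. The Sample size section sets 160 patients, 80 per arm, on expert advice, and aims to keep losses within 20%.

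**The concern.** When an outcome is measured before and after treatment, a two-sample t test makes poor use of the baseline. On post-treatment values it does not use the baseline at all. On changes it subtracts the whole baseline, whatever the correlation, which adds noise unless the correlation is high. ANCOVA estimates how much of the baseline to remove, so in large samples it is at least as precise as either. Leaving out the factors used for dynamic allocation also tends to make the test conservative when those factors predict outcome.

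The sample size rests on expert advice and not on a power calculation, so the analysis method is one of the few ways left to gain precision. What is at stake is the chance of detecting a real effect on LVEF, BNP, walking distance or Lee's score, and the width of the confidence intervals. BNP carries a second possible loss: if its distribution is right-skewed, a few high values dominate a raw mean, SD and t test.

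**Working it through.** **The plan's own figure.** 2 × 80 = 160, and 160 × 0.80 = 128 (64 per arm) if the full 20% is lost. The article gives no alpha, power, effect size, SD or correlation, so 160 cannot be reproduced from a power formula. The inputs below are therefore assumptions, apart from the arm sizes.

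**Step 1: relative variance of the treatment contrast** (equal SD before and after, correlation r):

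- post-value t test: 1
- change-score t test: 2(1 − r)
- ANCOVA: 1 − r²
- ANCOVA relative to change score: (1 − r²) / [2(1 − r)] = (1 + r)/2

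| r | Change score | ANCOVA | ANCOVA vs post value | ANCOVA vs change score |
|---|---|---|---|---|
| 0.3 | 1.40 | 0.91 | 9% lower | 35% lower |
| 0.5 | 1.00 | 0.75 | 25% lower | 25% lower |
| 0.7 | 0.60 | 0.51 | 49% lower | 15% lower |

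Against a post-value test, 160 patients analysed by ANCOVA work like 160/0.75 = 213 at r = 0.5 and 160/0.51 = 314 at r = 0.7. Those equivalents do not apply against a change-score test. There they are 160/0.75 = 213 and 160/0.85 = 188.

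**Step 2: power.** Assumed difference 0.4 SD, two-sided 5%, normal data:

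| Per arm | r | Post-value t | Change-score t | ANCOVA |
|---|---|---|---|---|
| 80 | 0.5 | 71.6% | 71.6% | 83.2% |
| 80 | 0.7 | 71.6% | 90.4% | 94.3% |
| 64 | 0.5 | 61.9% | 61.9% | 74.3% |
| 64 | 0.7 | 61.9% | 83.2% | 88.7% |

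**Step 3: BNP, if right-skewed.** Simulation with lognormal values before and after, correlation r on the log scale, treatment ratio 0.75, 80 per arm and no fall common to both arms. One run of 10,000 trials per setting gives:

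| Log-SD | r | Raw post t | Raw change t | Log-scale ANCOVA |
|---|---|---|---|---|
| 0.8 | 0.5 | 49% | 39% | 74% |
| 0.8 | 0.7 | 50% | 55% | 88% |
| 1.0 | 0.5 | 30% | 23% | 55% |
| 1.0 | 0.7 | 30% | 33% | 72% |

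Allowing for simulation error, the ranges are about 28-50%, 22-55% and 54-88%. Part of the gain comes from the scale alone: for post values, moving from a raw to a log t test raises power from 49% to 62% at log-SD 0.8 and from 30% to 43% at log-SD 1.0. The baseline adjustment supplies the rest. If BNP fell in both arms, the raw change test would do worse than shown; that is a further assumption and is not used here.

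**Step 4: validity.** With no treatment effect, the raw t test on lognormal post values rejects in 4.1% to 4.9% of simulated trials (log-SD 0.6 to 1.2, 64 or 80 per arm). The nominal 5% is not exceeded.

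**The case against.** The strongest reply is that the article only summarises and leaves detail to an SAP that is not shown. Covariates and transformations commonly belong there, and the SAP may already contain them. That stands as far as missing detail goes, and no omission is alleged here. But the article does name a test and a summary measure. An SAP that specified ANCOVA and log BNP would replace that statement, not fill it in, so the named method can fairly be compared with a better one.

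Four stronger readings are tempting, and the document does not support them.

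- *The t test could present a baseline imbalance as an effect, or be distorted because LVEF is capped at 40% on entry.* Chance imbalance is already counted in the 5% error rate. Regression to the mean acts on both randomised arms alike and does not bias the contrast. The cap does probably lower r for LVEF, which shrinks the gain over a post-value test.
- *Every objective endpoint is affected.* The trial also "analyzes the incidence and readmission rate for cardiovascular events", and these are rates, not t-tested. The primary analysis is not touched either: "The primary outcomes of the study include the effective rate on the improvement of heart functional class and TCM syndrome", so it falls under the chi-squared test. The TCM score would matter here only if analysed as a continuous value.
- *Baseline is ignored.* The Secondary outcomes section speaks of changes, so the change-score comparison is the fairer one.
- *BNP is known to be skewed.* The article gives no distribution. Skewness is an assumption here.

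**Conclusion.** The point holds as a matter of efficiency for LVEF, BNP, 6-minute walking distance, and Lee's score if treated as continuous. On the likelier reading, a t test on changes, ANCOVA lowers the variance by 25% at r = 0.5 and 15% at r = 0.7. If post-treatment values are meant, the reductions are 25% and 49%. These figures assume equal SDs before and after; r is not given in the article. ANCOVA is the more precise across the assumed range, but the size of the gain depends on r and on which t test is meant.

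The potential loss is largest for BNP, and it is conditional on skewness: under the lognormal assumptions in the working, log-scale ANCOVA has clearly higher power than either raw t test in all four settings.

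A reader might infer that the planned results would be invalid or biased. They would not be. This is a free improvement to secondary analyses, with no bearing on the primary outcomes or on type I error.

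**What to change.** In the SAP, make the main analysis of each continuous secondary outcome an ANCOVA of the post-treatment value on treatment, its own baseline value, age band and cardiac function class at baseline. Report the adjusted mean difference with a 95% CI. Analyse BNP on the log scale, with log baseline as covariate, and report the ratio of geometric means with a 95% CI; describe it by median and interquartile range. Keep the t tests as supportive analyses, and state whether they are on post-treatment values or on changes.

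The cost is SAP wording only. Baseline values and allocation factors are already collected, and the model uses only a few degrees of freedom from 160 patients. The Trial status section places the study at database testing, before the statistics, so the wording should be fixed before the treatment codes are opened. If the SAP already says this, only the statement in the article needs to be brought into line.

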## Methods

### Study design

This study is a prospective, randomized, multicenter, blind imitation, placebo-controlled trial. In order to avoid regional differences, participating centers include 12 hospitals located in the north and south of China. All cases included are hospitalized patients. Totally 160 subjects are randomly divided into treatment and control groups. The specific scheme is shown in Figure 1.

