### Sample size

This is a clinical pilot trial; therefore, the total sample size of this study is determined to be 160 (during the trial, the expulsion rate is controlled within 20%) on expert advice. The treatment group and the control group have the same number of cases (that is, there are 80 cases in each group).

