### Inclusion criteria

Patients aged 40 to 79 years;Diagnosis of CHD, AECHF;New York Heart Association Class II to IV;TCM diagnosis of *yang- qi* deficiency syndrome;Provision of written informed consent by participants or surrogates.

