### Randomization

This study will use the central randomization system of the Tianjin Institute of Clinical Evaluation to achieve the distribution of patients and drugs.

The central randomization system will adopt age (40 to 49, 50 to 59, 60 to 69, and 70 to 79 years) and cardiac function classification as the central random control factors to dynamically and randomly allocate the participants, keeping a balance between the two groups to avoid selection bias; it will also monitor the real-time drug distribution and inventory information of each center in order to timely supply drugs and effectively avoid drug excess, saving the resources of manpower and materials.

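### The only test named for the two primary effective rates ignores the factors used to balance allocation; it is conservative to the extent that those factors predict response

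*Protocol article*

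**What the plan says.** Three sections of the protocol bear on this point.

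- **Primary outcomes:** "The primary outcomes of the study include the effective rate on the improvement of heart functional class and TCM syndrome". Both are responder proportions, hence categorical.
- **Randomization:** the central system uses two control factors. One is "age (40 to 49, 50 to 59, 60 to 69, and 70 to 79 years"), that is, four bands. The other is class: "cardiac function classification as the central random control factors to dynamically and randomly allocate the participants". The inclusion criteria admit "New York Heart Association Class II to IV", so class has three levels.
- **Statistical analysis:** "Categorical variables will be presented using percentages and tested by chi-squared test". No stratification or covariate is named. The section then refers further detail to a formal statistical analysis plan, which is not at hand.

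On size, the Sample size section says "This is a clinical pilot trial; therefore, the total sample size of this study is determined to be 160", and "there are 80 cases in each group". It gives no significance level, power, expected rate or effect size.

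**The concern.** The design and the named test do not match. The ordinary chi-squared test takes its variance from allocation without restriction, where the arms may differ by chance on anything. Dynamic allocation removes most of the chance difference on age band and class. If those factors predict response, the observed difference in rates varies less from trial to trial than the test assumes. The standard error is then too large, the true type I error falls below its nominal level, and power is given up.

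Cardiac function class deserves attention here. It is the scale on which the first primary outcome is measured, so a patient's starting class may well affect the chance of being counted as improved. The protocol itself chose class and age as the factors to balance.

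At stake is some power in a trial of 160 whose size was set on expert advice, and intervals wider than they need be if they are built on the same variance.

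**Working it through.** **The plan's own figure.** The total of 160 is not derived from any rates or power, so there is nothing to reproduce.

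**Inputs from the protocol.** 80 per arm; dynamic allocation on four age bands and three classes; binary primary outcomes; unadjusted chi-squared test.

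**Assumptions (not in the protocol).** Two-sided 5% level; no continuity correction; 60% effective on control and 80% on treatment; class II/III/IV mix 20/45/35%; age-band mix 8/20/32/40%; minimisation with a 0.8 biased coin; no missing outcomes.

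**Step 1: reference power without prognostic factors.** The average rate is 0.70.

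- Null standard error: √(2 × 0.70 × 0.30 / 80) = 0.0725.
- Standard error under the alternative: √((0.60 × 0.40 + 0.80 × 0.20) / 80) = 0.0707.
- Power: Φ((0.20 − 1.96 × 0.0725) / 0.0707) = Φ(0.82) ≈ 79.4%.

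With 20% loss (80 × 0.8 = 64 per arm) the same formula gives 69.9%.

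**Step 2: the mechanism.** Let R² be the share of outcome variance explained by the balancing factors. The test assumes variance p(1 − p)(1/n₁ + 1/n₀); with the factors balanced, the true variance is about (1 − R²) times that. Hence

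true type I error ≈ 2 × [1 − Φ(1.96 / √(1 − R²))].

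Example at p = 0.60 and R² = 0.234: the assumed standard error is √(0.24 × 2/80) = 0.0775 and the true one is 0.0775 × √0.766 = 0.0678. The effective critical value is 1.96 / √0.766 = 2.24, which gives a type I error of about 2.5%.

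**Step 3: simulation.** 6,000 trials per scenario. The comparator is a linear-model test of treatment adjusted for both factors. Monte Carlo standard error is about 0.3 points on type I error and 0.5 points on power.

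| Prognostic strength (odds ratio per class / per age band) | R² | Type I error by formula | Type I error, chi-squared | Type I error, adjusted | Power, chi-squared | Power, adjusted | Power lost (points) |
|---|---|---|---|---|---|---|---|
| None (1.00 / 1.00) | 0 | 5.0% | 5.5% | 5.5% | 80.2% | 79.7% | −0.5 |
| Weak (1.49 / 1.22) | 0.027 | 4.7% | 4.9% | 5.4% | 80.1% | 80.3% | 0.2 |
| Moderate (2.23 / 1.49) | 0.096 | 3.9% | 4.1% | 5.0% | 81.2% | 83.0% | 1.8 |
| Strong (4.48 / 1.82) | 0.234 | 2.5% | 2.6% | 5.0% | 82.0% | 87.8% | 5.8 |
| Very strong (12.18 / 2.23) | 0.406 | 1.1% | 1.3% | 5.0% | 84.6% | 93.1% | 8.5 |

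Formula and simulation agree within simulation error.

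**Step 4: cost of stratifying finely.** A Cochran-Mantel-Haenszel test over all 12 class-by-age cells had power 78.2%, 78.8%, 81.8%, 86.9% and 93.1% in the same five scenarios. Against chi-squared it loses 2.0 and 1.3 points in the first two, gains 0.6 at moderate strength, and gains 4.9 and 8.5 in the last two. Stratification by class alone was not simulated.

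**The case against.** **The analysis plan may already deal with this.** The chi-squared sentence is a general rule for every categorical variable, and the protocol promises a fuller plan. An adjusted primary analysis may be written there. That stands as a caution, but it does not remove the point: the protocol does not leave the test open. It names one, and an adjusted analysis elsewhere would need to be reconciled with that sentence.

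**The effect is conditional and in the safe direction.** This stands. The documents do not say how strongly class or age band predicts response. Being the baseline of an outcome does not fix the size, or even the direction, of its effect on improvement. For the TCM syndrome rate the argument is weaker still. Type I error is not inflated, and with no stated power there is no target to miss.

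**Stronger readings that the documents do not support.**

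- A reader might infer that the p-values of both primary outcomes are simply wrong. With no or weak prognostic effect the chi-squared test performs as well as the adjusted one.
- A reader might expect a loss nearer 9 points already at strong prognostic strength. A further simulation (4,000 trials per scenario, fixed treatment odds ratio of 2.8, logistic score test) gave chi-squared power of 80%, 75% and 67% against 82%, 80% and 76%: gaps of 2, 5 and 9 points. But the adjusted test rejected 5.9% under the null in the last scenario, so part of that 9-point gap comes from a slightly liberal comparator. The fall from 80% to 67% is also mostly not due to the test, because at a fixed odds ratio the treated rate itself drops from about 81% to 77%.
- A reader might extend the point to centre, since the Study design section says "In order to avoid regional differences, participating centers include 12 hospitals located in the north and south of China". Centre is not a balancing factor, so the mechanism does not apply to it. Uneven splits within hospitals averaging 160/12 ≈ 13 patients are ordinary chance and do not invalidate the test. Changing the allocation is also probably moot, because the Trial status section places the study at database testing.

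**Conclusion.** The point holds in conditional form. The protocol balances allocation on age band and cardiac function class, then names for its primary rates a test that uses neither. The direction is secure: such a test is conservative if the factors are prognostic and is not materially anti-conservative in any scenario examined. The size is not secure. On the assumed 60% versus 80% with 80 per arm, the loss runs from nil to about 8.5 points of power, and true type I error from about 5% down to about 1.3%. The upper end needs odds ratios of roughly 4.5 to 12 per class, which nothing in the documents establishes. The case for acting is that a better-matched analysis costs almost nothing if the factors are weak and recovers several points if they are strong. The validity of the trial is not in question.

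**What to change.** Replace the general sentence, for the two primary effective rates, by a primary comparison that accounts for baseline cardiac function class and age band. Either of these would do:

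- a logistic model with treatment, baseline class and age band, reporting a standardised risk difference with its 95% confidence interval; or
- a Cochran-Mantel-Haenszel test stratified by baseline class. Crossing class with all four age bands is possible but costs 1 to 2 points of power if the factors turn out to matter little.

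Fix the choice, and have the analysis plan agree with it, before the data are analysed. Keep the plain chi-squared test as a sensitivity analysis. Because the logistic score test ran slightly above 5% in one simulated scenario, its type I error at this sample size is worth confirming when the test is chosen.

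The cost is a sentence in the protocol and in the analysis plan. Both covariates are already held in the randomization system, and the Trial status section describes the study as not yet at data entry and analysis.
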